### Intervention

#### OverThinking

OverThinking version 0.3.1(4) is a mobile EMI for iOS and Android platforms, designed to reduce EA in the context of rumination. The app primarily consists of psychoeducation content and related exercises, intended to be delivered over a 4-week period. To examine the effectiveness of the app during the intervention and to assess user experiences with using the app for rumination intervention, several self-report tools are embedded.

#### Development, Content, and User Evaluations

The development of the app was undertaken by a multidisciplinary team of active RFCBT practitioners; research psychologists with experience in transdiagnostic processes, digital mental health interventions, and user experience; and experienced developers of digital tools from the Polish-Japanese Academy of Information Technology.

The intervention comprises psychoeducational content based on RFCBT, an effective intervention for maladaptive rumination [86]. The reduction of EA is targeted through (1) the provision of a functional analysis of rumination to identify the triggers and functions of this process (a classical component of RFCBT), and (2) the modification of beliefs concerning negative emotions and their experience [87,88]. Previous research on the use of RFCBT has also found it to be an effective rumination intervention when delivered in digital contexts [89].

Intervention content was initially developed by members of our team with expertise in RFCBT. The content is divided into 4 weeks, with the first 2 weeks containing several individual modules targeting specific learning outcomes (eg, learning about the function of emotion, learning about the avoidance of emotions). The delivery of informative content is interspersed with several small exercises in different formats (multiple choice or open-ended text entry). Weeks 3 and 4 provide users with a series of exercises designed to consolidate learning and offer an opportunity for users to apply the psychoeducational content to their personal lives. Individual modules are designed to take no longer than 10-15 minutes to complete. The app content is delivered linearly, with subsequent weeks unlocking only once previous ones are fully completed. On each day of the intervention, all users are required to complete an emotion valuation question. All user inputs when completing app content are stored remotely and securely via Firebase (Google LLC), accessible only to the research team and solely for analysis purposes. In addition to user inputs and assessment outcomes, the time taken to complete app content and assessments is also recorded to observe the time burden caused by app use. A summary of the app intervention content can be found in Table 1.

**Table 1 table1:** Overview of intervention content.

Week, module, and module name				Module objectives
**Week 0**				
	**Module 1**			
		Introduction	To provide an introduction to the aims of the app. To introduce the daily assessments and their purpose.	
**Week 1**				
	**Module 1**			
		Introduction	To introduce the aims of module 1 (eg, to inform the user about the nature and function of emotions and their potential negative consequences).	
	**Module 2**			
		The nature of emotions	To examine the nature of depression and anxiety through individual dimensions (thoughts, emotions/feelings, and behavior) in users’ daily lives.	
	**Module 3**			
		The function of emotions	To examine the positive and negative functions of emotions.	
	**Module 4**			
		The avoidance of emotions	To examine the reasons for avoidance of emotions. To identify how users avoid negative emotions. To examine the consequences of avoidance.	
**Week 2**				
	**Module** **1**			
		Introduction	To introduce the second week, which places greater focus on rumination.	
	**Module** **2**			
		Ruminating	To identify and define rumination. Via fictional case studies, to identify situations in which users engage in rumination.	
	**Module 3**			
		Why do we ruminate?	To examine motivations for engaging in rumination. To identify some of the negative consequences of rumination.	
	**Module** **4**			
		Rumination and avoidance	To examine rumination as a means of avoidance/as an emotional regulation strategy.	
**Week 3**				
	**Module 1**			
		Introduction	To introduce the aims of the third and fourth weeks of the intervention—consolidation exercises to apply the psychoeducational content.	
	**Module 2**			
		Exercise 1	Identifying the content and context of the users’ ruminative thinking.	
	**Module 3**			
		Exercise 2	Identifying the triggers of the users’ ruminative thinking.	
	**Module 4**			
		Exercise 3	Identifying the short-term consequences of the users’ engagement in rumination.	
**Week 4**				
	**Module 1**			
		Exercise 1	Examining the use of rumination as a means of avoidance (and identifying what is being avoided).	
	**Module 2**			
		Exercise 2	Reducing/stopping the use of maladaptive rumination. Identifying activities that help users reduce their use of rumination.	
	**Module 3**			
		Exercise 3	Summarizing learning: identifying the context, content, consequences of users’ rumination, and how to reduce rumination and its maladaptive consequences.	

During the development process, an initial feasibility study was conducted to consult with prospective end users. Participatory workshops were held to obtain feedback on the usability and acceptability of the app content and to discuss preliminary plans for the app structure, visual layout, and features [69]. Before these workshops, participants, selected based on their rumination levels, were asked to engage with a web-based version of the proposed app content (hosted via Qualtrics; SAP SE) for 4 weeks. Participants were asked to complete a series of pre- and posttests online, designed to mimic the randomized controlled trial protocol for this trial (see the “Methods” section, except for the BEAQ measure). A series of attentional tests was also included in the online assessment to control for response reliability. To be included in the analysis, participants were required to complete the first 2 weeks of content in full, followed by 5 of the 6 exercises from weeks 3 and 4.

Of the initial 687 participants who registered interest in participating, a sample of 55 was selected through prescreening using the PTQ. Participants were selected if their overall score was 1 SD above average. Of these, 21 participants completed all measures and were included in the quantitative analysis. Four participants volunteered to engage in participatory workshops and took part in semistructured interviews with members of the research team. The semistructured interviews focused on (1) factors determining compliance and strategies to overcome challenges in following the 4-week program; (2) strong and weak aspects identified in the program content; (3) accessibility of psychoeducational content in terms of language, clarity, and length; (4) strong and weak aspects of the user experience; (5) evaluation of different exercise types; and (6) evaluation of a mock-up for apps, with users having previous experience following the 4-week program.

Overall, data from the developmental feasibility study suggested that engagement with app content resulted in reductions in EA (comparison of pre- and postintervention measures; *P*<.001) and perseverative thinking (*P*<.001), including across all 3 subscales: mental load (*P*=.001), unproductiveness (*P*=.003), and core features (*P*=.002). While cognitive avoidance did not reduce significantly overall (*P*=.07), the descriptive reduction suggested an impact of the psychoeducational program on awareness. Thought substitution was significantly elevated after participation (*P*=.06), which may indicate increased awareness of this mechanism.

Because of the small sample size for participatory workshops, the data were not subjected to a formal analysis protocol and are unlikely to have reached saturation at this stage. However, feedback indicated that users found the intervention content and exercises interesting, with some participants reporting that they would have preferred more content to engage with. Additionally, participants requested that the app include an option to make personal notes invisible to the research team, provide links to additional information relevant to rumination and avoidance, and allow for text narration and audio recordings as alternatives to text entry.

Following user feedback, the app was updated to include a link providing further information about the research and the research team, along with relevant content details and additional external resources. Future versions of the app aim to incorporate further personalization options, such as voice narration, audio recording features, and a private notes function.

#### Remote Acquisition/Storage of Assessment Data

Data obtained through daily sampling are securely stored remotely via Firebase and are accessible only to authorized members of the research team, in compliance with General Data Protection Regulation (GDPR) requirements.

To capture user experiences during testing, the app also uses the CORTO method [82]. These data are likewise securely stored via Firebase and are accessible only to members of the research team.

### Statistical Analysis

#### Data Exclusion

Compliance will be defined as the completion of both the first and second weeks of the intervention content in full, along with at least 5 out of 6 exercises from weeks 3 and 4. For EMA, a compliance threshold of 80% will be used, consistent with previous research using EMIs in adult populations [90]. Additionally, the study will control for time spent within the app and the length of responses to open-ended questions.

In addition to the aforementioned compliance measures, participants who fail both attentional checks embedded within the assessments will be excluded from analyses.

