**Figure 1 figure1:**
[figure not shown]
Graphical representation of the randomized controlled trial protocol. CBT: cognitive behavioral therapy; RNT: repetitive negative thinking.

Participants will be randomly assigned, using a random-number generator, to 1 of 4 conditions: (1) intervention condition (therapist support); (2) intervention condition (no therapist support); (3) partial intervention (daily sampling and emotion valuation questions); or (4) control group (only daily sampling questions). Active control groups will be utilized to avoid artificially inflating comparisons with intervention condition outcomes [64]. The specific group allocations and the nature of other study conditions will be concealed from participants. Block/random stratification will not be used, as participants will be randomly allocated to 1 of the groups after agreeing to participate in the study. During analysis, demographic characteristics across groups will be compared, and any significant differences identified will be included as control variables.

Therapist support has been shown to improve outcomes in studies of digital mental health interventions [61]. In this study, therapist support will take the form of asynchronous written communication with a cognitive behavioral therapy (CBT) practitioner—either fully qualified or in at least their second year of training—via WhatsApp (Meta Platforms, Inc). This support will be available 2 times a week to relevant participants at specific times predetermined by the therapist. Participants will have the option to utilize this support, but will not be directed to do so. Supporting therapists will be paid at their standard hourly rate for regular patients and will receive an introduction to the app and intervention—while remaining blinded to the full aims of the study—through an online workshop conducted by members of the research team experienced in delivering rumination-focused cognitive behavioral therapy (RFCBT), before the study.

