### Recruitment Strategy

Participants will be recruited through online advertising on social media platforms (Facebook/Instagram; Meta Platforms, Inc) and via the laboratory website, where a contact email address will be provided for interested individuals to express their interest in participating. Full study information will be sent by email to all interested participants, and informed consent will be obtained via email response before the delivery of the app and the commencement of participation. To minimize information sharing across groups, participants will not have access to one another’s contact or identity details. Additionally, the current version of the app does not allow users to contact other participants or to determine how many others are using the app.

Recruitment is expected to begin in early May 2025 and will continue until the target number of participants in each condition has been reached. Participants may withdraw from the study at any time by contacting the research team via a designated email address provided in the study information form or through a link within the app. All data associated with participants who choose to withdraw will be fully removed from the study and destroyed. Participants will receive financial compensation of €50 (US $56) for taking part in the study.

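### Data Exclusion, on its best reading, selects participants on post-randomisation behaviour, partly by a content rule that can operate only in arms 1 and 2, and withdrawals' data are destroyed

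*Protocol article*

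**What the plan says.** The Data Exclusion subsection of Statistical Analysis sets three rules in sequence.

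- **Content.** "Compliance will be defined as the completion of both the first and second weeks of the intervention content in full". A second condition allows no more than one of the six later exercises to be missed.
- **Daily assessment.** "For EMA, a compliance threshold of 80% will be used". Ecological Momentary Assessment gives 30 days of prompts, so the threshold is 24 days.
- **Attention checks.** "In addition to the aforementioned compliance measures, participants who fail both attentional checks embedded within the assessments will be excluded from analyses". Pre-Post and Follow-Up Measures places two such checks in the pre, post and follow-up assessments.

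Study Design gives arm 3 daily sampling with emotion valuation questions and arm 4 daily sampling alone. Control participants receive the app content only after the 1-month follow-up. Primary Outcomes then compares all four conditions by mixed-design ANOVA and asks, in multilevel models, whether condition moderates the daily associations.

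On withdrawal, Recruitment Strategy says: "All data associated with participants who choose to withdraw will be fully removed from the study and destroyed".

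**The concern.** Randomisation makes the four arms comparable at the start. A rule that removes people for what they do afterwards keeps that comparability only if it removes the same kind of person, in the same proportion, from each arm. The content rule cannot do that, because arms 3 and 4 have no modules to finish. Applied only where modules exist, it trims arms 1 and 2 alone; applied literally, nobody in arms 3 and 4 qualifies. Neither version gives a usable four-arm randomised comparison. The rule is also demanding, since each week unlocks only after the previous one is fully completed.

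The daily-assessment and attention-check rules reach all arms, but they too act after randomisation, and their effect can differ by arm.

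If people who persist with the content are also those who would have improved anyway, the trimmed intervention arms look better with no effect of the app. Study Design chose active controls so that the comparison would not be inflated; arm-specific exclusion can bring the inflation back. Destroying withdrawals' data is irreversible, so no later analysis plan could restore those participants.

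**Working it through.** **1. Does the text make compliance an exclusion rule?** Three things point that way: the subsection heading; the wording that joins attention-check exclusion to the compliance measures as an addition; and the feasibility study described under Development, Content, and User Evaluations. There the same content rule (first two weeks in full, 5 of 6 exercises) was the stated condition for entering the analysis, in testing designed to mimic this trial.

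**2. The plan's own sample size.** The article gives 60 for 4 groups, 3 time points and a medium effect. Alpha, power and the correlation among repeated measures are not stated. Taking f = 0.25, alpha 0.05, correlation 0.5, sphericity and power 0.95, the group-by-time interaction has λ = f²·N·m/(1−ρ) = 0.0625 × 60 × 3 / 0.5 = 22.5, with 6 and 112 degrees of freedom. Power is 0.954 and 60 is the required N. The point therefore does not rest on an error in that figure.

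**3. Numbers per arm.** Recruiting double, 120, gives 30 per arm. The article cites about 60% attrition in the feasibility study, where 21/55 = 38% were analysed. At 40% kept, a content arm falls from 30 to 12 (30 × 21/55 = 11.5). An arm keeping 80% has 24; one keeping everyone has 30.

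**4. Size of the selection effect when there is no true effect.** Assume compliance follows a standard normal tendency correlated r with improvement, and each arm keeps its most compliant fraction p. The mean tendency among those kept is i(p) = φ(z)/p, where z cuts off the top fraction p.

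- i(0.40) = 0.966
- i(0.80) = 0.350
- i(1) = 0
- Spurious difference in change = r × [i(p in arms 1–2) − i(p in arms 3–4)]

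| r | 40% v 80% kept | 40% v 100% kept |
|---|---|---|
| 0 | 0 | 0 |
| 0.2 | 0.2 × 0.616 = 0.12 SD | 0.2 × 0.966 = 0.19 SD |
| 0.3 | 0.3 × 0.616 = 0.18 SD | 0.3 × 0.966 = 0.29 SD |
| 0.4 | 0.4 × 0.616 = 0.25 SD | 0.4 × 0.966 = 0.39 SD |

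**5. False-positive rate.** This comes from 3,000 simulated null trials per scenario, 30 randomised per arm, one change score, nominal 5%.

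| r | Arms 1+2 v 3+4, controls keep 80% | Same, controls keep all | Four-group F, controls keep 80% | Same, controls keep all |
|---|---|---|---|---|
| 0 | 0.05 | 0.05 | 0.04 | 0.05 |
| 0.2 | 0.08 | 0.11 | 0.06 | 0.09 |
| 0.3 | 0.11 | 0.21 | 0.08 | 0.13 |
| 0.5 | 0.23 | 0.53 | 0.15 | 0.34 |

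The correlations and the retention in arms 3 and 4 have no source in the article.

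**The case against.** **Exclusion for non-compliance is inferred.** The only explicit exclusion clause attaches to the attention checks. The abstract gives the content definition without any exclusion, and the Discussion presents compliance as a measure of engagement. This stands: exclusion is the best reading, not an explicit statement, and confidence is moderate for that reason.

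**Not every rule is arm-specific.** A reader might infer that only the app-content arms can fail the rules. That is true of the content rule alone. All arms do daily sampling, face the attention checks and may withdraw.

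**The 38% is not retention under the content rule.** The article says: "Of these, 21 participants completed all measures and were included in the quantitative analysis". That count combines unfinished content with missing questionnaires, which control arms also face, and it comes from a web-based version. The 40% is therefore an assumption.

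**The control arms are not known to stay whole.** A reader might infer that nearly all controls are kept. The 24-of-30-day threshold argues against that, so the 100% column is an upper case.

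**The bias depends on correlation with change.** A stable correlation with outcome level cancels in the group-by-time test. Nor does a mean-shift calculation describe the multilevel slopes. Both points stand.

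**A separate analysis plan may define an all-randomised set.** It may, so silence on that is not the finding. The finding rests on the exclusion and destruction rules this document does state.

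**Destruction covers active withdrawal only.** It applies to those who withdraw by email or the app link. The documents do not support reading it as erasing everyone who simply stops.

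**Conclusion.** The concern holds in this form. On its best reading, Data Exclusion selects participants by three kinds of post-randomisation behaviour before the four-arm comparison. One of them, content completion, can select only within arms 1 and 2. Withdrawals' data are lost for good in every arm; that loss is differential only if withdrawal differs by arm, but it always prevents a complete all-randomised analysis.

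The size is illustrative: 0.12 to 0.25 SD for correlations of 0.2 to 0.4 with 40% and 80% kept, 0.19 to 0.39 SD as the upper case, and zero at zero correlation. It assumes that better compliers improve more; the opposite sign would reverse the bias. Bias in the multilevel slopes is not quantified. The article does not show that a spurious benefit will occur, only that the stated rules leave the comparison open to one. Confidence is moderate.

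**What to change.** In Data Exclusion:

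- Make the primary set all randomised participants, analysed as randomised with all available data, for example in a mixed model that uses partial data.
- Use the content rule and the 80% daily-assessment threshold only to describe adherence and to define a labelled per-protocol sensitivity analysis. The multilevel models accept unequal numbers of days per person and do not need the threshold.
- Apply attention-check exclusion only to the pre-randomisation assessment, or as a sensitivity analysis.

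In Recruitment Strategy, keep data collected up to withdrawal unless the participant asks for erasure, as consent and ethics approval allow. Keep arm and date of withdrawal for the flow count.

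The cost is analysis wording, a sentence in the participant information and a notice to the ethics committee. The estimated effect may be smaller than among compliers. The withdrawal change needs to be in place before enrolment, because destroyed data cannot be recovered.

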**Methods:**

Consenting individuals (target N=60) who meet the inclusion criteria (self-reporting problems with repetitive negative thinking) will be randomly assigned to 1 of 4 conditions: (1) intervention with therapist support and daily sampling, (2) intervention without support and with daily sampling, (3) partial intervention (emotion validation EMI only) with daily sampling, or (4) control (daily sampling only). The intervention consists of a series of modules delivered over 4 weeks, with assessments conducted before and after intervention, and again at 1-month follow-up (plus an additional 3-month follow-up for intervention participants). Data will be collected both through online self-report assessments and via the app itself. The potential of the EMI to modify the maladaptive feature of repetitive negative thinking will be assessed using mixed-design ANOVA, while the links between avoidance-mood and rumination-mood, in terms of the moderating effect of trial condition, will be evaluated using multilevel models. These will be assessed as primary outcomes. Secondary outcomes are the effects of a supporting therapist on postintervention outcomes in the intervention groups, and time spent using the app as a measure of engagement (analyzed using the mixed-design analysis of covariance). Compliance will be defined as completing both of the first 2 weeks of intervention content in full, and 5 out of the 6 exercises from weeks 3 and 4. Additionally, the study will control for both the amount of time spent in the app and the length of responses to open-ended questions.

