#### Analysis of Trial Outcome Data

##### Primary Outcomes

Changes in outcomes across pre-, post-, and follow-up assessments (PTQ, EBQ, PBRS, NBRS, HADS, CAQ, and BEAQ) will be analyzed using mixed-design ANOVA across all 4 conditions. Additionally, multilevel models—treating daily observations as level 1 and participants as level 2—will be used to assess associations between avoidance and mood, as well as between rumination and mood, and to examine whether these associations are moderated by condition.

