##### Secondary Outcomes

Mixed-design analysis of covariance will be conducted within the 2 intervention groups to examine whether time spent engaging with the app content serves as a covariate influencing intervention outcomes.

In-app user feedback collected through the CORTO method will be deductively coded following the process outlined by Saldana [91], using the 4 overarching categories proposed by Lukka et al [82]—(1) contextual use, (2) interaction-elicited emotional experience, (3) usability, and (4) technical issues—as a guiding framework. More detailed subdomains will be explored within each category.

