The incorporation of CORTO implementation enables the collection of real-time feedback from users regarding app usability and acceptability, addressing some of the limitations of retrospective interviews [82]. This approach acknowledges the central role of users as active participants in the treatment program and enhances the specificity of the feedback obtained [94]. As CORTO depends on sustained engagement with the digital tool under review, authors recommend considering survivorship bias when interpreting the data [82].

To address some of the limitations associated with using retrospective measures alone, the effectiveness of the intervention will also be assessed by analyzing daily sampling measures, as recommended by Heron and Smyth [43]. Additionally, we plan to compare the standalone version of the intervention with one that includes asynchronous support from CBT professionals. A recent meta-review of meta-analyses [95] suggested that guided interventions may be more effective and improve compliance; however, it notes that the quality of evidence is often low and that not all meta-analyses systematically compare the impact of guidance. Therefore, it is important to explore the effect of guidance. While including professional support can significantly enhance the intervention’s effectiveness, it also increases the cost of large-scale implementation and limits its potential for widespread dissemination. For this reason, a compromise solution involving asynchronous support was chosen.

The outcomes of the trial will be reported in a peer-reviewed publication following the mHealth Evidence Reporting and Assessment guidelines, as outlined by the World Health Organization mHealth Technical Evidence Review Group [96]. These guidelines are designed to enhance the quality and clarity of mHealth evaluation reporting by specifying where detailed information should be provided regarding intervention content, implementation context, and relevant technical aspects.

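### The unrestricted promise to control for app time and response length, both consequences of allocation, must be kept out of every between-arm comparison

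*Protocol article*

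**What the plan says.** Under Statistical Analysis, Data Exclusion, after the compliance rules, the protocol article states that "the study will control for time spent within the app and the length of responses to open-ended questions". The Abstract (Methods) repeats this after describing the primary and secondary analyses and the compliance definition: "the study will control for both the amount of time spent in the app and the length of responses to open-ended questions". Neither sentence is tied to an analysis.

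The analysis sections are narrower. Under Primary Outcomes, the questionnaire scores "will be analyzed using mixed-design ANOVA across all 4 conditions", and multilevel models of the daily data are used "to examine whether these associations are moderated by condition". No covariate is named for either. Under Secondary Outcomes, app time appears as a covariate: "Mixed-design analysis of covariance will be conducted within the 2 intervention groups to examine whether time spent engaging with the app content" influences outcomes. The Abstract lists the effect of therapist support and time in the app together as the secondary outcomes, and names the same covariance analysis there.

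Study Design describes what each arm receives. Arms 1 and 2 get the full intervention, with and without therapist support. Arm 3 gets daily sampling with emotion valuation questions. Arm 4 gets daily sampling only.

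**The concern.** Time in the app and length of open text are measured after randomisation, and what the arm offers largely determines both. Holding them equal across arms compares people who would not be comparable under randomisation alone. The result then does not estimate the effect of being allocated to the intervention.

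The document itself treats engagement as a route to benefit. The account of the feasibility study attributes reduced experiential avoidance to engagement with the content. The Discussion worries that moving through the content too fast would weaken its impact. On support, the Discussion notes that "guided interventions may be more effective and improve compliance", so app time plausibly lies between therapist support and outcome. At stake are the main four-arm result and the therapist-support result, each resting on about 15 people per arm (60 divided by 4).

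**Working it through.** **What each arm can generate.** Table 1 lists 1 module in week 0, 4 in each of weeks 1, 2 and 3, and 3 in week 4: 1 + 4 + 4 + 4 + 3 = 16. On length, the article says: "Individual modules are designed to take no longer than 10-15 minutes to complete". The ceiling is therefore 16 x 10 = 160 to 16 x 15 = 240 minutes of content in arms 1 and 2. Arms 3 and 4 do not receive this content, but they do spend time in the app on daily sampling. The described open-text entries sit in the module exercises, and the open user-experience item follows in-app exercises. Response length therefore depends on the arm as well.

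**What adjustment does.** Let the total effect of allocation be T, the mean difference in app time between the compared groups D, and the within-group slope of outcome on app time g. In a linear model without interaction:

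- adjusted effect = T - g x D
- with equal halves and within-arm SD of time s, variance factor = 1 + 0.25 x D²/s². This ignores any outcome variance that app time explains.

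The slope g mixes the causal effect of time with anything that drives both time and outcome, such as motivation or severity.

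**Illustration.** The document gives none of D, s, g or T. Assume T = -0.50 outcome SD (lower is better), D = 150 minutes and s = 40, 60 or 100 minutes, with two intervention arms against two comparison arms and 15 per arm. The shared-cause rows assume no mediation, with loadings of 0.5 on time and 0.4 on outcome, so g = ±0.2/s. For s = 40 with more time going with better outcome, the formula gives -0.50 + 0.2 x 150/40 = +0.25. A simulation of 2,000 trials per scenario gave:

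| Quantity | s = 40 | s = 60 | s = 100 |
|---|---|---|---|
| Variance factor | 4.52 | 2.56 | 1.56 |
| SE factor (square root) | 2.12 | 1.60 | 1.25 |
| Adjusted effect, all through app time | -0.03 | -0.02 | 0.01 |
| Half through app time | -0.27 | -0.24 | -0.24 |
| None through app time | -0.52 | -0.49 | -0.51 |
| Shared cause, more time with better outcome | +0.26 | 0.00 | -0.19 |
| Shared cause, more time with worse outcome | -1.27 | -0.99 | -0.80 |

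The unadjusted estimate was about -0.50 throughout, with standard error about 0.26.

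**Other comparisons.** For arm 1 against arm 2 the same formula applies, with D the extra app time that support produces. If support changes app time, the adjusted contrast omits that route. In the multilevel models, the condition-by-rumination term is exposed in the same way if usage is given the matching interaction.

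**Sample size.** The stated 60 is reproduced by the within-between interaction test with 4 groups, 3 time points, f = 0.25, correlation 0.5, alpha 0.05 and power 0.95 (power at 60 is 0.954). The article states only a medium effect, so these settings are inferred. The calculation has no covariate in it, so the fix does not change it.

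**The case against.** The strongest reply is that no sentence says the four-arm comparisons will be adjusted. The Primary Outcomes section names no covariate, and the authors switch from ANOVA to covariance analysis only for the two intervention arms. The sentence sits among compliance rules, and the account of the feasibility study uses similar wording for attention checks on response reliability. It could therefore mean data-quality screening. Covariate lists are also commonly left to an analysis plan that is not shown. The four-arm ANOVA already contains arms 1 and 2 without a named covariate, and the stated aim of the secondary analysis is to learn "whether time spent engaging with the app content serves as a covariate influencing intervention outcomes", not to produce an adjusted therapist effect.

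Much of this stands. A reader might infer that the primary models will certainly be adjusted, and the document does not establish that. Nor does it support zero app time in arms 3 and 4, since every arm does daily sampling. Whether those arms also enter open text cannot be checked, because the daily items are in an appendix that is not shown.

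The other readings do not rescue the sentence. Screening on usage is itself selection after randomisation, on variables that the arms do not generate alike. Confining the sentence to the secondary analysis still places app time in the only analysis specified for the two intervention arms, with which the Abstract lists the therapist outcome, and leaves response length in no described analysis. The point is also not a missing detail: the rule is stated, twice, without limits.

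**Conclusion.** The concern holds as a conflict between an unrestricted rule and analysis sections that do not carry it. If the rule is followed in any between-arm comparison, including support against no support, the estimate is not the effect of allocation. It loses the part that runs through engagement, the remainder may be biased either way, and precision falls.

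It would go too far to say that adjustment removes the effect being tested. That happens only if the whole effect runs through the adjusted variables. With half mediated, half remains; with none mediated and no shared cause, only precision is lost. The figures (+0.26 to -1.27 around a true -0.50, and a standard error 1.25 to 2.1 times as large) rest on the assumed time gap, spread, mediation split and loadings. They show what is possible and do not predict this trial's result. The arm dependence itself, up to 160-240 minutes of content in two arms only, comes from the document.

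**What to change.** Replace the sentence in Data Exclusion and in the Abstract with a scoped one: the four-arm ANOVA, the multilevel moderation models and the comparison of therapist support with none are neither adjusted for, nor screened on, time in the app or length of open-ended responses. State that the therapist-support effect is estimated as a total effect, without app time in the model. Report app time and response length by arm as adherence outcomes. Keep the covariance analysis under Secondary Outcomes as an exploratory association between time and outcome within the intervention arms, labelled as non-causal.

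The cost is analysis wording only. No data collection changes, and the target of 60 is unaffected.
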